## Abstract

**Background:**

Total laryngectomy (TL) is a surgical procedure commonly performed on patients with advanced laryngeal or hypopharyngeal carcinoma. One of the most common postoperative complications following TL is the development of a pharyngocutaneous fistula (PCF), characterized by a communication between the neopharynx and the skin. PCF can lead to extended hospital stays, delayed oral feeding, and compromised quality of life. The use of a myofascial pectoralis major flap (PMMF) as an onlay technique during pharyngeal closure has shown potential in reducing PCF rates in high risk patients for development of PCF such as patients undergoing TL after chemoradiation and low skeletal muscle mass (SMM). Its impact on various functional outcomes, such as shoulder and neck function, swallowing function, and voice quality, remains less explored. This study aims to investigate the effectiveness of PMMF in reducing PCF rates in patients with low SMM and its potential consequences on patient well-being.

**Methods:**

This multicenter study adopts a randomized clinical trial (RCT) design and is funded by the Dutch Cancer Society. Eligible patients for TL, aged ≥ 18 years, mentally competent, and proficient in Dutch, will be enrolled. One hundred and twenty eight patients with low SMM will be centrally randomized to receive TL with or without PMMF, while those without low SMM will undergo standard TL. Primary outcome measurement involves assessing PCF rates within 30 days post-TL. Secondary objectives include evaluating quality of life, shoulder and neck function, swallowing function, and voice quality using standardized questionnaires and functional tests. Data will be collected through electronic patient records.

**Discussion:**

This study’s significance lies in its exploration of the potential benefits of using PMMF as an onlay technique during pharyngeal closure to reduce PCF rates in TL patients with low SMM. By assessing various functional outcomes, the study aims to provide a comprehensive understanding of the impact of PMMF deployment. The anticipated results will contribute valuable insights into optimizing surgical techniques to enhance patient outcomes and inform future treatment strategies for TL patients.

**Trial registration:**

NL8605, registered on 11-05-2020; International Clinical Trials Registry Platform (ICTRP).

## Introduction

Total laryngectomy (TL) is performed routinely in patients with primary advanced laryngeal or hypopharyngeal carcinoma with invasion of the thyroid or cricoid cartilage and/or extra laryngeal soft tissue. TL is also indicated in patients with residual or recurrent disease after treatment with chemoradiation or radiotherapy solely and patients with a dysfunctional larynx due to posttreatment sequalae. During TL, the distinction between the swallowing and breathing pathways is established by forming both a neopharynx and a tracheostoma. A pharyngocutaneous fistula (PCF) is one of the most common postoperative complications after TL and is defined as a saliva-leaking communication between the neopharynx and the skin (see Fig. 1). PCF mostly exists between the mucosal line of the neopharynx and the surgical skin incision or, but less frequently, around the tracheostoma [1, 2]. Incidence rates vary between 6% and 58% in literature [3]. In a nationwide Dutch study an overall incidence rate of 26% in 324 patients undergoing TL was found [4].

**Fig. 1 Fig1:**
[figure not shown]
Simplified image of the neopharynx, a pharyngocutaneous fistula, myofascial and myocutaneous pectoralis major flap

PCF is associated with severe consequences such as prolonged hospital stay and delay or interruption of the start of oral feeding and voice rehabilitation, leading to a long healing course significantly impacting the patient’s quality of life [5–7]. In addition, PCF may cause complications such as carotid artery rupture or delay of the needed adjuvant treatment, potentially jeopardizing optimal oncologic treatment [4–8]. PCF has even been associated with an increased risk of distant metastases after TL salvage [9].

Conservative treatment of PCF usually consists of local wound treatment and antibiotics, and the patient is fed by a nasogastric tube or parenteral nutrition. However, due to the breakdown of the mucosal suture and therefore the constant flow of saliva into surrounding soft tissues, wound healing is often impaired. Surgical closure of PCF after failure of the conservative treatment is indicated in 37–58% of the patients [2, 7, 10]. In summary, preventing PCF holds the potential to minimize the influence of the negative outcomes on the patient’s quality of life, help to avoid additional surgeries and their associated morbidity and reduce the risk of life-threatening complications.

One of the surgical strategies to minimize PCF development following TL is the transfer of a myofascial pectoralis major flap (PMMF) to the neck as onlay for reinforcement of the pharyngeal closure (see Fig. 1) [11]. It has been shown that a prophylactic PMMF reduces the risk of PCF in TL patients significantly [12–14] or PCFs were smaller and less likely to require surgical repair [11–15]. Prophylactic PMMF has also demonstrated to decrease a patient’s morbidity and hospital stay and results in financial savings for the healthcare system [16].

Several risk factors for PCF have been described in literature such as prior chemoradiotherapy, the extent of the pharyngectomy, neck dissection, pre-treatment tracheostomy, preoperative albumin and low BMI [3, 4, 17, 18]. A nationwide Dutch study showed a broad range of PCF incidence between the centers of the Dutch Head and Neck Society (NWHHT), which could not be fully explained by the prediction model developed with known risk factors know at that time. More recently also, a preoperative radiological assessed low skeletal muscle mass (SMM) was found to be an independent risk factor for PCF development [18, 19].

In recent years, research on body composition and especially on SMM has increased. It appears that a low SMM is associated with acute and late adverse events in patients with head and neck cancer during (chemo)radiotherapy [20–23], flap-related complications [24, 25], decreased survival rates [26–29], and PCF [18, 19]. This emphasizes the importance of considering SMM in assessing PCF risk.

Therefore, in this randomized controlled trial (RCT), our primary aim is to investigate if the use of PMMF as onlay on the pharyngeal closure for reinforcement will reduce the PCF rate in TL patients with a high risk for PCF because of low SMM.

## Methods and analysis

### Objectives

#### Primary objective

To determine and compare among patients with low SMM, the PCF rate in those with PMMF as onlay for reinforcement to the PCF rate in those without PMMF. PCF rate will also be evaluated in patient without low SMM and in patients who unexpectedly needed the PMMC for reconstruction of the pharynx.

#### Secondary objective(s)

Secondary outcome measurements will only be scored in the group with low SMM. In this group, the following outcomes are compared between the group with and without PMMF using questionnaires and function tests.

Quality of life.Shoulder and neck function.Swallowing function and dysphagia complaints.Voice quality and it’s psychological consequences.Patient’s perspective.The healthcare related costs.

### Study design and population

This multicenter PECTORALIS-study is designed as a randomized clinical trial (RCT) and funded by the Dutch Cancer Society (KWF) (NL72319.041.20).

Patients who are planned for TL, will be included in this study when they: (1) have a minimum age of 18 years, (2) are mentally competent and (3) have sufficient knowledge of the Dutch language to be able to give informed consent. Patients will be enrolled by their head and neck surgical oncologist and/or by a researcher after consultation in one of the participating tertiary referral centers of the NWHHT or three Belgian (Dutch speaking) centers. Patients will be excluded for this study when they: (1) will be treated with chemoradiotherapy (with cisplatinum/carboplatin) for a previously diagnosed head and neck carcinoma (HNC), (2) will undergo TL with reconstruction of the pharynx with myocutaneous pectoralis major (PMMC), gastric pull up or jejunal flap, (3) have major CT- or MRI-scan artefacts impeding accurate muscle tissue identification, and (4) have an interval between TL and imaging longer than 2 months.

When a patient is eligible for participation in this study, SMM will be measured using routinely performed (FDG-PET/)CT- or MRI scan of the head and neck as described below (see Fig. 2).

**Fig. 2 Fig2:**
[figure not shown]
Timeline of including patients

After informed consent, patients with low SMM will be centrally randomized between prophylactic PMMF at the time of TL or not. A stratified permuted-block procedure randomizes patients to the groups on a 1:1 ratio. Strata include treating center and concomitant neck dissection. Both primary and secondary outcome measurements as described below will be evaluated in the group with low SMM.

Patients without low SMM will undergo the TL as regularly scheduled, will not be randomized and only the primary outcome measurement will be evaluated.

Patients definitively scheduled for TL with reconstruction of the pharynx using the PMMC meet the exclusion criteria and thus will not be recruited for the study. If in an included patient, regardless of SMM and possible randomization, it is unexpectedly decided peroperatively that a PMMC is required for reconstruction of the pharynx, these patients will be followed over time. The primary outcome measurement will still be evaluated.

In conclusion, the primary outcome measure is thus evaluated in the following groups:

Patients with a low SMM who will undergo a TL with PMMF.Patients with a low SMM who will undergo a TL without PMMF.Patients without a low SMM who will undergo TL as regularly scheduled.Patients who unexpectedly need a PMMC for reconstruction of the pharynx during the TL, regardless of their SMM.

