### Statistical analysis

Our primary hypothesis is that the use of PMMF as onlay for reinforcement can reduce the PCF rate in patients with low SMM after TL from 31.0 to 9.9%. To test this hypothesis, we will compare the incidence of fistula formation in patients with low SMM between the group with PMMF (intervention arm) and the group without PMMF lap (control arm) by the Chi-squared test or when needed the Fisher’s exact test (N < 5). To demonstrate the association between SMM and fistula formation, the incidence of fistula formation in the control arm (low SMM without PMMF) will be compared with the incidence of fistula formation in the (non-randomized) group of normal SMM. The relative risk will be calculated with an associated 95% confidence interval. Modified Poisson regression models will be used to correct for potential confounder, such as radiotherapy in prehistory, type of closure of the neopharynx etc.

Results of our other outcomes will be presented as the mean scores with standard deviation for continuous variables or as median with interquartile range for ordinal or non-normal distributed continuous data. Differences between groups with or without PMMF will be tested by independent t-tests for normally distributed continuous data and for ordinal and non-normal distributed continuous data Mann Witney U tests will be used. Differences over time within groups with or without PMMF will be tested by paired t-tests for normally distributed continuous data and for ordinal and non-normal distributed continuous data Wilcoxon signed-rank tests will be used.

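### Randomised patients who unexpectedly receive a PMMC are listed as a separate primary-outcome group, and the plan does not say that they stay in their allocated arm for the primary test

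*Protocol article*

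**What the plan says.** The Study design and population section (text after Figure 2) places randomisation before surgery: "After informed consent, patients with low SMM will be centrally randomized between prophylactic PMMF at the time of TL or not". Allocation is 1:1: "A stratified permuted-block procedure randomizes patients to the groups on a 1:1 ratio".

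The same section then deals with conversion during the operation: "If in an included patient, regardless of SMM and possible randomization, it is unexpectedly decided peroperatively that a PMMC is required". Such patients are followed, and "The primary outcome measurement will still be evaluated". The section ends with a list of the groups in which the primary outcome is evaluated: low SMM with PMMF, low SMM without PMMF, no low SMM, and "Patients who unexpectedly need a PMMC for reconstruction of the pharynx during the TL, regardless of their SMM".

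The Primary objective section makes the same separation: "PCF rate will also be evaluated in patient without low SMM and in patients who unexpectedly needed the PMMC for reconstruction of the pharynx". The Primary outcome measurement section repeats it. The Statistical analysis section sets the primary test "between the group with PMMF (intervention arm) and the group without PMMF lap (control arm"), by chi-squared or Fisher's exact test. No section says in which arm a randomised patient who received a PMMC is counted for that test.

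**The concern.** The fourth group is formed by an event that happens after randomisation. Taking randomised patients out of their arm because of such an event gives up the protection of randomisation unless the event is unrelated to both allocation and outcome. Neither can be assumed here.

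- **Allocation.** The decision is made in theatre, and nothing in the article says that the surgeon is unaware of the allocation at that point.
- **Outcome.** The Introduction names the extent of the pharyngectomy as a risk factor for PCF, so patients who turn out to need a pharyngeal reconstruction may differ in fistula risk from those who do not.

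If conversions differ between arms in number or in risk, the remaining patients are no longer comparable. The trial also has few events, so a handful of reassigned patients carries weight.

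**Working it through.** **1. Is removal the natural reading?** Four features of the article point that way.
- The conversion rule applies regardless of possible randomisation, so it reaches randomised patients.
- The fourth group cuts across SMM status. If converted low-SMM patients also stayed in the first two groups they would be counted twice, and nothing says so.
- A PMMC patient fits neither the label with PMMF nor the label without PMMF.
- The Power calculation section takes its 31.0% control rate from a database after excluding patients with pharyngeal reconstruction. The sizing therefore assumes a comparison without such patients.

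**2. The plan's own figure.** Inputs from Power calculation: 31.0% v 9.9%, 61 per arm, two-sided alpha 0.05, power 85%, pooled Z-test. Summing the two binomial distributions over all outcomes that the pooled Z-test rejects gives exact power of 84.7% at 61 per arm (normal approximation 83.2%). The stated power reproduces within about 2 points. Expected fistulas are 61 × 0.310 = 18.9 (19) and 61 × 0.099 = 6.0 (6).

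**3. Sensitivity of the primary test.** Pearson chi-square without correction, z = (p1 − p2) / √[p(1 − p)(1/n1 + 1/n2)], with p the pooled rate. With no conversions, 19/61 v 6/61 gives z = 2.92, p = 0.0035. The number and outcome of converters below are assumptions.

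| Assumed converters | Converters removed | Analysed by allocation |
|---|---|---|
| 3 in PMMF arm, 1 fistula | 19/61 v 6/58, p=0.005 | 19/61 v 7/61, p=0.008 |
| 3 in PMMF arm, 2 fistulas | 19/61 v 6/58, p=0.005 | 19/61 v 8/61, p=0.016 |
| 3 in PMMF arm, 3 fistulas | 19/61 v 6/58, p=0.005 | 19/61 v 9/61, p=0.031 |
| 4 in PMMF arm, 4 fistulas | 19/61 v 6/57, p=0.006 | 19/61 v 10/61, p=0.056 |
| 3 in each arm, same number of fistulas in each (0 to 3) | 18/58 v 6/58, p=0.006 | 18/61 v 6/61 to 21/61 v 9/61, p=0.006 to 0.012 |

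Only the fourth row changes the conclusion at 0.05.

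**4. Bias without a treatment effect.** Suppose both arms have a true rate of 31%, and a share s of patients with fistula rate q is removed from one arm only. That arm's rate becomes (0.31 − s·q)/(1 − s). With s = 10%, q = 50%: 0.26/0.90 = 28.9%, a spurious difference of 2.1 points. With s = 15%, q = 60%: 0.22/0.85 = 25.9%, a difference of 5.1 points. All values of s and q are assumed.

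**5. Power under the two analyses.** Assume a share e converts in each arm.
- Removed: n per arm is 61(1 − e).
- Kept: the arm rates become (1 − e)·0.310 + e·r and (1 − e)·0.099 + e·r, where r is the fistula rate in converters, taken as equal in both arms and between 20% and 50%.

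| e (assumed) | Removed: n per arm, exact power | Kept at 61 per arm: exact power |
|---|---|---|
| 5% | 58, 83.4% | 78.5–80.6% |
| 10% | 55, 81.0% | 71.7–76.0% |
| 15% | 52, 78.5% | 64.6–70.9% |

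Analysis by allocation therefore costs more power than removal.

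**The case against.** **No sentence removes these patients from the chi-squared test.** This is true. The Primary objective wording is additive, the list is not called exclusive, and the primary test names its groups as intervention and control arm, which is the language of allocation. The analysis population is also commonly settled in a fuller protocol or an SAP, neither of which is shown. This limits the point to how the stated text reads, but does not remove it: the article does not merely stay silent, it sets converted patients apart in three sections and never returns them to an arm.

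**The numerical illustration is a worst case.** This also stands. The change in conclusion needs four conversions in one arm only, with a fistula in every one.

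**Stronger readings that the documents do not support:**
- A reader might infer that a promise of intention to treat is broken. The article makes no such promise.
- A reader might infer that conversion is easier in the PMMF arm because the muscle is being raised anyway. The Intervention section has the neopharynx closed first and describes the flap harvest after that, so this mechanism finds no support. Possible knowledge of the allocation is enough for the concern.
- A reader might see the same flaw in the exclusion of patients who "have an interval between TL and imaging longer than 2 months". That is an enrolment criterion, which can be checked against the planned surgery date, and nothing applies it after randomisation.

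**Conclusion.** The point holds as a defect in the stated grouping for the primary outcome. The most natural reading takes randomised low-SMM patients out of the primary comparison because of an intraoperative decision, and the text should not leave that open. The size and direction of the bias are unknown, because the documents give neither a conversion rate nor the fistula risk of converters. In the extreme illustration the conclusion turns (p=0.006 against p=0.056). Under the milder assumptions shown it does not. The loss of power from removal is small at an assumed 5% conversion (84.7% to 83.4%), so the reason to act is comparability of the arms and not sample size. A reader might conclude that the primary result is bound to be biased or in favour of PMMF; nothing in the documents supports that.

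**What to change.** 1. State in the Study design and population and the Statistical analysis sections that the primary test includes every randomised low-SMM patient in the allocated arm, whatever flap is used in theatre.
2. Report the number of PMMC conversions by arm.
3. Keep the PMMC group, including its randomised members, as a descriptive group, and add a sensitivity analysis of the primary comparison without converters.
4. Add a caveat to the Power calculation: converters kept in their arms dilute the effect. At an assumed 5% conversion, exact power at 61 per arm is about 78–81%, and it falls further at higher rates. An expected conversion rate should be stated.

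Items 1 to 3 cost wording only, since the primary outcome is already collected in these patients. Item 4 discloses a modest loss of power. The text should be settled before outcomes are compared between arms. None of this bears on when a PMMC should be used.

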### Measurement of SMM

The cross-sectional area (CSA) of the paravertebral muscles and both sternocleidomastoid muscles at the level of the third cervical vertebra (C3) will be measured by using (FDG-PET/)CT or MRI. When possible, CT is preferred over MRI because you are aided in accurately delineating the CSA by setting the radiodensity to -29 and + 150 Hounsfield Units (HU) which is specific for muscle mass [30, 31]. If MRI-imaging is used, SMM will be manually delineated, excluding fatty mass through manual means. If FDG-PET/CT is available, SMM will also be measured (directly) at the level of the third lumbar vertebra (L3). The single axial slide at level C3 of imaging which will show both the transverse processes and the entire vertebral arch scrolling from cranially to caudally will be selected. This segmentation of SMM will be performed using the software package SliceOmatic (Tomovision, Canada). CSA at level of C3 will be converted to the CSA at L3 by using the formula as previously described by Swartz et al [30] Then the CSA at L3 will be corrected for height thus creating the lumbar skeletal muscle index (LSMI). A LSMI of ≤ 43.2 cm2 /m2 will be considered as low SMM.

### Intervention

First the neopharynx will be closed. The PMMF will be harvested by elevating the muscle off the chest like the myocutaneous pectoralis major (PMMC) flap, but without the skin and subcutaneous fat of the donorsite (see Fig. 1). Then the muscle and its fascia will be tunneled into the neck and sutured to different structures around the neopharynx. In this manner, the PMMF will be used as a muscular vascularized flap and additional layer to cover the delicate closure of the neopharynx [11, 32].

### Outcome measurements

#### Primary outcome measurement

As mentioned above, the PCF-rate following TL will be scored in patients with a low SMM who will undergo a TL with or without PMMF, without low SMM (undergoing TL as regularly scheduled) and in patients who unexpectedly need a PMMC for reconstruction of the pharynx during the TL, regardless of their SMM.

PCF is defined as a clinical fistula requiring any form of conservative or surgical treatment occurring within 30 days after TL. To also assess the prevention of possible PCF development, the results of the swallow X-ray and their potential impact on the patient’s oral intake are taken into account. This approach aims to obtain the most comprehensive evaluation of PCF incidence.

#### Secondary outcome measurements

In low SMM patients shoulder and neck function, swallowing function, and voice quality with their consequences on quality of life (QoL) will be investigated by questionnaires before and 6 months after TL.

The following questionnaires will be assessed:

Quality of life: European Organization for Research and Treatment for Cancer Quality of Life Questionnaires, EORTC QLQ-C30, EORTC-QLQ-H&N35, and EuroQol 5D 5 L (EQ-5D-5 L) [33–35].Shoulder and neck function: the Shoulder Disability Questionnaire (SDQ) [36], Shoulder Pain and Disability Index Dutch Language Version (SPADI-DLV) [37] and the Neck Disability Index (NDI) [38].Swallowing function and dysphagia: The Dysphagia Severity Scale (DSS) and Dysphagia Quality of Life Scale (DQOL), after laryngectomy the Swallow Outcomes After Laryngectomy (SOAL) [39], the M.D. Anderson Dysphagia Inventory (MDADI) [40] and the Functional Oral Intake Scale (FOIS) for dysphagia (the only investigator reported outcome measurement (IROM)) [41].Voice quality: Voice Handicap Index (VHI) [42].

Shoulder and neck function tests will be performed depending on the feasibility in the participating center also before and 6 months after TL. In addition, this latter group of patients will be recruited 3 months after TL to have a voice recording and a video fluoroscopy (VFSS). Performance of these side studies will also be performed on the available logistics of the participating center.

